**7 METHODS AND STUDY PROCEDURES**

**7.1 Study sites and personnel**

*7.1.1 Selection of study sites*

Study sites in each country will be health centers, either government-run or private/missionary, that provide routine antenatal and peri-natal care. The health centers for this evaluation will be selected on the basis of the following characteristics: representation from a range of malaria transmission and geographic zones within Africa; interest and capacity of local researchers and public health authorities; accessibility from the collaborating research team’s base; interest and capacity of the health center staff; and patient numbers adequate to allow enrollment of the target sample size within a period of approximately 6 months. On the basis of current information and preliminary agreements, selected sites include: Colsama government health center in District de Dô, a peri-urban area near Bobo-Dioulasso, Burkina Faso (seasonal transmission); St Kizito Catholic Hospital and/or Regina Mundi Catholic Hospital, Lagos, Nigeria (low year-round transmission); and Tororo District Hospital in eastern Uganda (high year-round transmission). If for unforeseen reasons we are unable to conduct the evaluation at the specific centers listed, alternative sites will be chosen to preserve the representative range of geography and malaria endemicity.

*7.1.2 Personnel conducting protocol activities*

For the purposes of this study, routine antenatal and delivery care will be provided by the staff of participating health centers, i.e. health workers who are employed by the health center (all participating health centers are either government- or missionary-sponsored established health facilities). Such health workers typically include midwives, nurses, and other similar cadres of health care staff. In this protocol, these personnel are referred to as “health center staff.”

Study-specific activities will be conducted by personnel hired for the purposes of the research study, i.e. individuals employed by the study coordinators. Throughout this protocol, this personnel group is referred to as “study staff.” Study staff will typically be individuals with laboratory and/or clinical background and with prior experience in clinical malaria research. Both health center staff and study staff will be trained in the protocol and relevant study procedures prior to the start of the study, and at each site the personnel groups will work together to achieve the study goals while ensuring smooth continuation of care. Further details for each site will be described in the site-specific protocols.

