**11.1 Study outcome measures**

Results of peripheral blood tests performed during gestation will be analyzed for associations with evidence of placental malaria and pregnancy outcomes. The statistical analysis will focus on three primary outcomes: 1) negative predictive power of malaria RDTs, peripheral blood films and PCR performed on peripheral blood to diagnose placental malaria during gestation, 2) association of placental malaria during gestation on mean infant birth weight and 3) association of placental malaria during gestation on mean maternal Hb. These outcomes will be used to assess the potential utility of RDTs as screening tests to identify clinically significant malaria infections at a time when effective preventive measures may be taken. Other factors known to influence the study outcomes, including iron and folate supplementation, bed net use and administration of antihelminthic drugs will be treated as confounders in the analysis. In addition, stratified analysis will be conducted to assess these associations within subgroups based on geographic location, estimates of malaria endemicity, participant age, and parity (gravida class).

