**11.3 Sample size considerations**

The target sample size for the number of participants at each study site is calculated to test the hypothesis Ho: [PPV ≤ (disease prevalence + α) or NPV ≤ (1-disease prevalence)] with 80% power and 5% significance at each study location. For the higher transmission sites of Uganda and Burkina Faso α=0.4, while α=0.3 for Nigeria. Previously published estimates of sensitivity (65%) and specificity (98%) were used in these calculations.

Using the target sample sizes outlined below the study will be powered to detect changes in infant birth weight and maternal Hb of >85g and 0.34g/dl, respectively. The sample size for the Burkina Faso site should also allow detection of changes in infant birth weight (>123g) with sufficient power. Based on published data, other sites will not be individually powered to detect likely changes in birth weight (~123g) and none of the sites will be individually powered to detected likely changes in maternal Hb (~0.4g/dl). However this will not prohibit any of the statistical analysis planned.

We estimate that the statistical requirements of the study can be met by enrolling 345 women at the high-transmission Ugandan site, 460 women at the low-transmission Nigerian site, and 860 women at the seasonal-transmission site in Burkina Faso, for a total sample size of 1,665 participants. This estimate assumes a 15% loss to follow-up at each study location.

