**11.4 Participant enrollment and follow-up**

Recruitment and enrollment will include all eligible pregnant women who present for routine antenatal care in their second or third trimester (sections 6, 7.2.1). Recruitment will continue at each site until the target sample size given in Section 9.3 is reached.

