**15 DURATION OF THE PROJECT**

The duration of participant recruitment and follow-up is expected to take approximately 12 months from the start of study activities at each site, depending on rates of enrollment.

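### The largest site has seasonal transmission, but no confounder, stratum or accuracy analysis uses month or season, so its results depend on when recruitment happens to fall

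*Protocol*

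**What the plan says.** Protocol section 7.1.1 names three sites and gives each a transmission pattern. Burkina Faso is "a peri-urban area near Bobo-Dioulasso, Burkina Faso (seasonal transmission"); the Nigerian and Ugandan sites are both described as year-round. One criterion for choosing health centres is "patient numbers adequate to allow enrollment of the target sample size within a period of approximately 6 months".

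Section 11.3 sets targets of 345 for Uganda and 460 for Nigeria. The largest target is "860 women at the seasonal-transmission site in Burkina Faso, for a total sample size of 1,665 participants". Section 2 adds that funds are in hand only for Burkina Faso and Uganda.

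Section 11.4 states: "Recruitment will continue at each site until the target sample size given in Section 9.3 is reached". (The target stands in section 11.3; there is no section 9.3.) It attaches no calendar condition. Section 15 says recruitment plus follow-up is "expected to take approximately 12 months from the start of study activities at each site, depending on rates of enrollment".

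On the analysis:
- Section 11.1 stratifies by "subgroups based on geographic location, estimates of malaria endemicity, participant age, and parity (gravida class"). It names iron and folate, bed nets and antihelminthics as confounders.
- The table in section 11.2, introduced as the complete data set per woman, classes as confounders study site, age, gravidity, SP treatment, iron and folate, and bed net use.
- Accuracy is to be estimated pooled and by site.
- Birth weight and haemoglobin are compared between women who were RDT positive and those who were RDT negative.

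No month, season or other calendar variable appears in any of these places.

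**The concern.** Seasonal transmission means that the risk of infection changes within the year. At such a site, the season in which a woman is tested bears on whether her RDT is positive and on whether she is infected during pregnancy. Two planned analyses are exposed.

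**Outcome comparison.** RDT-positive and RDT-negative women are not randomised groups. If positives cluster in the transmission months, the groups differ in calendar time. Anything else that varies over the year and acts on birth weight or haemoglobin then enters the comparison, and none of the listed covariates removes it.

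**Predictive values.** NPV is part of the first primary outcome in section 11.1. PPV and NPV depend on prevalence, and the section 11.3 null hypothesis is itself written in terms of prevalence. A single Burkina Faso figure is an average weighted by the season mix recruited. It does not show how screening performs at different times of the year, although section 11.1 wants it to inform the usefulness of RDT screening.

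**Working it through.** **Inputs from the protocol.** Targets 860, 345 and 460, sensitivity 65%, specificity 98%, loss to follow-up 15%, and a birth-weight difference of more than 123 g that Burkina Faso should be able to detect (all section 11.3). Funded sites: Burkina Faso and Uganda (section 2).

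**Site weight.** 345 + 460 + 860 = 1,665, which reproduces the stated total. Burkina Faso is 860/1,665 = 52% of all three sites and 860/(860 + 345) = 860/1,205 = 71% of the funded two. Expected completers are 860 × 0.85 = 731.

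**Could an existing variable stand in for season?** Study site cannot, because the variation is within one site. The endemicity stratum is listed beside geographic location and reads as a contrast between sites. Age, gravidity, SP treatment, supplements and bed net use are characteristics of the woman or her care.

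**Predictive values.** The protocol gives no prevalence for any site or season, so 5% and 30% are assumptions. For prevalence p:
- PPV = 0.65p / (0.65p + 0.02(1 − p))
- NPV = 0.98(1 − p) / (0.98(1 − p) + 0.35p)

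| Assumed p | PPV | NPV |
| --- | --- | --- |
| 5% | 0.0325/(0.0325 + 0.0190) = 0.631 | 0.931/(0.931 + 0.0175) = 0.982 |
| 30% | 0.195/(0.195 + 0.014) = 0.933 | 0.686/(0.686 + 0.105) = 0.867 |

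The dependence on the recruitment mix follows from the same assumptions:
- 20% of women from the high season: p = 0.2 × 0.30 + 0.8 × 0.05 = 10%. PPV = 0.065/0.083 = 0.783; NPV = 0.882/0.917 = 0.962.
- 80% from the high season: p = 0.8 × 0.30 + 0.2 × 0.05 = 25%. PPV = 0.1625/0.1775 = 0.915; NPV = 0.735/0.8225 = 0.894.

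The test and the site are the same in both cases; only recruitment timing differs.

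**Outcome comparison.** Assume RDT positivity of 30% in the high season and 10% in the low season, with half the women enrolled in each.
- High-season share of RDT-positives: 0.15/(0.15 + 0.05) = 75%.
- High-season share of RDT-negatives: 0.35/(0.35 + 0.45) = 44%.
- Spurious difference: (0.75 − 0.4375) × 100 g = 31 g for each 100 g by which birth weight differs between seasons for other reasons.

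With high-season shares of 20%, 50% and 80%, and positivity pairs of 30%/10%, 40%/10% and 25%/15%, the result runs from 9 to 40 g per 100 g. The 100 g is a unit for scaling; the documents give no seasonal birth-weight difference.

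**The case against.** **The list is open, and a SAP may exist.** Section 11.1 gives its confounders as examples, so season could be added later. That is fair, but nothing requires it. The protocol itself sets out the complete data set, classifies each variable and names the strata, and it leaves out the feature by which it distinguishes its largest site.

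**Six months is not a window.** A reader might infer that enrolment is confined to six months and that one season is bound to be over-represented. The text does not support this. The six months is a criterion for choosing sites, recruitment runs until the target is met, tests and deliveries spread over about 12 months, and no start date is given. What stands is that the season mix is left to chance.

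**The definitions blur the mechanism.** A reader might infer that a low-season test followed by a high-season delivery lowers the planned NPV by a definite amount. Section 11.2 counts a woman as RDT positive if any of her samples is positive, including the one at delivery, so a later infection can still be caught. Its reference standard is also cumulative: PCR on any peripheral sample, or histology, which covers prior as well as current infection. Both soften the seasonal contrast. The sequence applies more directly to primary objective 2, which sets tests in gestation against histology.

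**The planned hypothesis need not fail.** At the assumed values the expected PPV and NPV exceed their null limits in both seasons: 0.631 > 0.45 and 0.982 > 0.95 at 5%; 0.933 > 0.70 and 0.867 > 0.70 at 30%. These are expectations, not power. The concern is what the estimate means, not a predicted failure of the test.

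**A fine split is too thin.** Season of test crossed with season of delivery gives four cells of about 731/4 = 183 women. At 5% prevalence that is about 9 infected women per cell. This objection stands in full, and the fix avoids that split.

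**Conclusion.** The point holds as an unadjusted source of confounding and averaging at the site that dominates the funded study. The site labels, the 71% share, the stopping rule without a calendar condition and the absence of season from the confounders, strata and accuracy analysis are all in the protocol.

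The size is not. The gap of about 30 points in PPV and 11 in NPV rests on assumed prevalences of 5% and 30% and on treating disease status as prevalence in the season of test; under the planned definitions it would be smaller. The 9 to 40 g per 100 g rests on assumed positivity rates. It also needs birth weight to vary by season for reasons other than the woman's own infection, which the documents neither state nor quantify. It would therefore be wrong to conclude that the birth-weight or haemoglobin result is biased by a known amount or in a known direction. The change is worth making because it is cheap and fits models already planned.

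**What to change.** 1. Add transmission season (or calendar month) of enrolment and of delivery to the confounders in the section 11.2 table, and to the marginal models for predictive values and the regression models for birth weight and haemoglobin.
2. For Burkina Faso, show the distribution of enrolments and deliveries by month, so that the mix behind the site figures is visible.
3. For Burkina Faso, report the accuracy of the tests done in gestation against placental histology (primary objective 2) by season of test. Present this as a descriptive stratum, without a further split by season of delivery.

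**Cost.** The change is to the analysis text. Section 7.5 already records the date of birth and of delivery samples, and antenatal visit dates are needed to keep the visit spacing in section 7.3.5. The models lose a few degrees of freedom. Intervals within seasons will be wider: with equal halves, about 731/2 = 366 women per season, or about 18 infected women in a season with an assumed 5% prevalence. That is why the stratum should stay descriptive.

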**7.2 Study enrollment**

*7.2.1 Selection for recruitment and enrollment*

At each site, pregnant women will be invited to enroll in the study when they present to the participating health center for routine antenatal care. At each site, potential participants will be referred by health center staff to study staff, and will be screened and enrolled by study staff according to the selection criteria listed in section 6. At each participating site, information on current health status, obstetric history, and chronic conditions including HIV infection (see selection criteria 6-9 in section 6 above) are collected by health center staff as part of routine antenatal care. HIV counseling and testing is routinely offered to all pregnant women on an opt-out basis at each site. Study staff will conduct screening interviews with each potential participant after she has completed her antenatal visit for that day. Study staff will rely on health center staff’s diagnosis of these conditions in determining whether a potential participant meets all selection criteria. In case of questions about whether a participant meets all criteria on medical grounds (e.g. presence or absence of chronic disease), study staff will confer with health center staff, and where appropriate with the potential participant, to reach a final decision on whether to offer enrollment.

***Uganda site-specific information (as requested by WHO; italic font):*** *At the Uganda study site (Tororo District Hospital, TDH), women presenting for routine antenatal care are first welcomed at the reception desk of the ANC in the hospital compound. At the reception desk, each attendee is registered in the ANC book, including general information such as name, age, pregnancy status, and residence. If an attendee is pregnant and aged 16 to 44 years (inclusive), the health center reception staff will notify her that she may be eligible for this study, and ask if she would like to learn more about the study. If she agrees, she will be invited to talk in a private area of the ANC with a member of the study staff responsible for obtaining informed consent. If she declines to learn more about the study, or declines participation after the consent discussion, she will have no further contact with study staff, and will continue her antenatal visit as usual with health center staff. If she agrees to participate, she will sign or fingerprint the informed consent form (see section 7.2.2) and will continue with her antenatal visit as usual and including the study activities described in section 7.3. Newly enrolled study participants will undergo the usual routine antenatal screening and care provided at TDH (see further details below).*

***(End Uganda site-specific information.)***

Those women who are screened and found to be ineligible for the study on medical grounds (i.e. selection criteria 6-9 and 11) will be managed according to routine practice by health center staff. At each site, HIV counseling and testing is linked to an established treatment program to reduce mother-to-child HIV transmission. Other acute or chronic conditions are managed on-site as capacity allows, or referred to a higher level of the health care system according to local guidelines.

***Uganda site-specific information (as requested by WHO; italic font):*** *As a matter of routine, information pertaining to the age, gestational status, HIV status, and medical and obstetric history is obtained by health center staff during typical antenatal visits at TDH. In particular, as a matter of routine and Uganda national policy, all antenatal attendees are invited to undergo HIV testing. If a potential participant declines routine HIV testing, she will no longer be eligible for the study; she will be so informed, she will not participate in any further study activities, and she will continue with the usual care available at TDH. If a participant agrees to the routine HIV testing and tests negative, she will continue with routine care at TDH and with study activities as described below. If a participant agrees to the routine HIV testing and tests positive, she will no longer be eligible for the study; she will be so informed, she will not participate in any further study activities, and she will be referred to local HIV health care providers for appropriate care. HIV care at the TDH site is typically provided through The Aids Support Organization (TASO), a well-established service which provides counseling, advice and materials for prevention of mother-to-child transmission, prophylaxis of opportunistic infections according to national guidelines, antiretroviral therapy according to national guidelines, and other appropriate services.*

*In addition to HIV, other medical conditions or history may render a potential participant ineligible for the study, including history of adverse reactions to antimalarial drugs, history of obstetrical complications, history or presence of chronic disease, etc (see selection criteria Section 6 and Appendix C Enrollment form). For women who have signed the informed consent form, after completion of the antenatal visit, study staff will confer with the woman and the health center clinician to confirm whether the woman meets all selection criteria. If so, a study staff member with laboratory training will check the participant’s hemoglobin level as in Sections 7.3.2 and 7.6.1. If all selection criteria are met, the participant will be considered fully enrolled and will continue with study activities as described in Section 7.3. If any selection criterion is not met, the participant will no longer be eligible for the study; she will be so informed, she will not participate in any further study activities, and she will continue with the usual care available at TDH.*

***(End Uganda site-specific information.)***

*7.2.2 Provision of written informed consent*

Each participant will provide written informed consent (Appendices A and B) at the time of enrollment. A trained study staff member will conduct individual screening interviews and informed consent discussions with potential study participants. Informed consent will be conducted in the potential participant’s preferred language, with the assistance of a translator if necessary. Consent forms, approved by all relevant ethical review boards, will be available in English (Nigeria, Uganda) or French (Burkina Faso) and in the local language/s for each site. If the participant is unable to read or write, her fingerprint will be substituted for a signature, and a signature from a witness to the informed consent procedures will be obtained. Potential participants will have the opportunity to ask questions and discuss details of the study with study staff, and are free to ask further questions at any time during or after completion of the study activities. In the case of participants under the age of 18, international49 and country-specific guidelines on the inclusion of minors in research (including guidelines related to emancipated minors, and/or co-consent from a parent or guardian) will be strictly followed to allow participation by individuals in this vulnerable group, and therefore to allow the future application of data and potential benefits from this study to the same.

***Uganda site-specific information (as requested by WHO; italic font):*** *Ugandan guidelines on parental consent for pregnant minors, and related risks, are as follows. According to the National Guidelines for Research Involving Humans as Research Participants of the Uganda National Council for Science & Technology (UNCST), published March 2007, section 9.3 on Mature and Emancipated Minors states: “Mature minors are individuals 14-17 years of age who have drug or alcohol dependency or a sexually transmitted infection; while emancipated minors are individuals below the age of majority who are pregnant, married, have a child or cater for their own livelihood. Mature and emancipated minors may independently provide informed consent to participate in research if: a. In the view of the IRC the research is not objectionable to parents or guardians (established by the IRC with evidence from the community); b. The research protocol includes clear justification for targeting mature and emancipated minors as participants; and a clear justification for not involving parents or guardians in the consent process.”*

*For the purposes of this study, and as discussed with UNCST personnel, this study will take the following approach: For biological, scientific and ethical reasons, pregnant women/girls aged 16-44 years (who meet all selection criteria) will be eligible for this study.  To be useful, the study results should be applicable to the general population of pregnant women/girls in malaria-endemic areas; as pregnancy before age 18 is not uncommon in these areas, the study should include participants from the younger age range, in order to provide representative results.  In addition, participants may (or may not) benefit from study participation, and that potential benefit should be extended to typical primigravidae as well as older women. Pregnant participants aged 16-17 are minors, and may be considered “mature and emancipated minors” according to the UNCST guideline. For informed consent purposes, we will therefore consider two categories for 16-17 year-olds who wish to participate in the study:*

*a) A prospective minor participant comes to the ANC with her parent, or with a guardian figure (older sibling, husband, etc).  In this case we will seek both written assent from the minor, and written consent from the adult parent/guardian.*

*b) A prospective minor participant comes to the ANC alone, and wishes to consent for her own participation.  In this case, we will seek only her written consent, as she is considered a mature and emancipated minor.*

